### Data analysis

The intent-to-treat (ITT) analysis set will include all subjects who are randomized into a surgery group. The modified ITT analysis set will include all subjects who undergo pre-CRT. The per protocol (PP) analysis set will include only the subjects in the ITT group who complete the study protocol. Patients who withdraw informed consent or who develop serious adverse events will be excluded from the PP analysis set. The modified ITT set will be used for analysis of primary and secondary study endpoints. The PP analysis set will be used for subgroup analysis. Baseline characteristics will also be analyzed in the ITT group.

Variables and outcomes will be analyzed using chi-square tests (for proportions) or Fischer’s exact test, as appropriate. Continuous data will be analyzed using Student’s t-test or Mann-Whitney U tests, as appropriate. Cumulative risk rates will be calculated using the Kaplan-Meier method and compared using log-rank tests. Multivariate analyses using binary logistic regression will be used to assess the risk of postoperative complications. Statistical significance will be defined as *p* < 0.05, and all analyses will be performed using SPSS software, version 22 (IBM Corporation, Armonk, NY, USA).

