### Study population

Patients who were diagnosed with pathologically confirmed rectal adenocarcinoma < 8 cm from the anal verge with clinically T3 or N+ before pre-CRT and an mrTRG grade 1 or 2 based on post-CRT images will be eligible for the study when they meet the following inclusion criteria:Male and female patients between the age of 20 and 80;Good performance status (ECOG performance status < 2);Capable of providing informed consent.

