### Pre-registration procedures

#### Preoperative chemoradiotherapy

Pre-CRT was delivered at 50.4 Gy to the primary tumor and the pelvis in 25 fractions. Concurrent chemotherapy during radiotherapy consisted of 5-fluorouracil (5-FU; 375 mg/m^2^/day) and leucovorin (LV; 20 mg/m^2^/day) or capecitabine (825 mg/m^2^). 5-FU and LV were given on three consecutive days for two courses during the first and fifth weeks of radiotherapy, while capecitabine was given twice daily during the entire radiotherapy period without a weekend break.

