#### Sample size calculation

The sample size was calculated based on two-sided non-inferiority test with for 80% power and a significant level of 0.05, one-sided. We assume that the rate of postoperative complications on day 30 will be 15% in the TME group and 15% in the LE group, with a non-inferiority margin of 15%. Based on these calculations, a total of 67 patients should be allocated to each group; assuming a 5% dropout rate, we plan to enroll 140 patients. The 15% rate of postoperative complications cited above is based on published findings [26–28, 30].

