#### Randomization and data management

After checking the response of pre-CRT, the participants with mrTRG 1 or 2 tumor will be assigned using random-number table with sealed envelopes by an external research worker who control the data. According to mrTRG 1 or 2, the allocation sequence will be stratified. The external research worker will collect the data and a statistician who provided the sample size calculation and data analysis plan will be analyze the data. The data entry, coding, security and storage with backup will be processed by the external research worker and simultaneously the statistician will check the accuracy and the value of the data. After finishing the collection of data, the external research worker, the statistician will access the dataset and investigators will access after analyses of the dataset.

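### The modified ITT set named for the primary and secondary endpoints is defined by pre-CRT, which comes before randomisation, so it cannot work as a modified ITT set

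*Protocol article*

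**What the plan says.** The Data analysis section of the protocol article defines three sets. For the first: "The intent-to-treat (ITT) analysis set will include all subjects who are randomized into a surgery group". For the second: "The modified ITT analysis set will include all subjects who undergo pre-CRT". The third, the per-protocol set, is drawn from the ITT group. The section then says which set serves the endpoints: "The modified ITT set will be used for analysis of primary and secondary study endpoints". The ITT set is kept for baseline characteristics and as the parent of the per-protocol set, which is used for subgroup analysis.

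Other sections fix the order of events. Pre-CRT is described under the heading "Pre-registration procedures". Study population says that patients with "an mrTRG grade 1 or 2 based on post-CRT images will be eligible for the study". Randomization and data management says: "After checking the response of pre-CRT, the participants with mrTRG 1 or 2 tumor will be assigned using random-number table with sealed envelopes". Table 1 places permission, screening and the serial number at restaging, 4–8 weeks after pre-CRT.

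Two further passages bear on the fix. Under Investigational treatment of the experimental arm, an LE patient who goes on to TME is counted with the TME group, and one who declines a recommended TME leaves the study and is followed for a separate subgroup analysis. Secondary study endpoints, item 4, is the predictive accuracy of mrTRG.

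**The concern.** A modified ITT set normally starts from the randomised patients and removes some of them by a stated rule. Here the defining event happens before randomisation, so it cannot distinguish one randomised patient from another. The wording also carries no restriction to randomised patients.

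This is the set named for the 30-day complication endpoint, on which the non-inferiority comparison and the sample size rest. If the definition is left as it stands, someone must decide after the fact who belongs in the primary denominator. In an open-label trial that decision should not be open once outcomes are known.

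**Working it through.** No stated figure in the article depends on this definition, so the check compares the sections and reasons from them.

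**1. Order of events.**

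| Step | Source |
|---|---|
| Pre-CRT given | Pre-registration procedures |
| Restaging with MRI; permission and serial number | Preoperative restaging; Table 1 |
| Eligibility: mrTRG 1 or 2 on post-CRT images | Study population |
| Allocation to LE or TME, stratified by mrTRG 1 or 2 | Randomization and data management |
| Surgery | Table 1 |

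**2. Sets.** Let *C* be the patients who had pre-CRT and *R* the randomised patients (the ITT set). Eligibility needs a post-CRT image, so every eligible randomised patient has had pre-CRT: *R* lies inside *C*.

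**3. Literal reading.** Modified ITT = *C*. It contains *R* plus everyone in *C* who was not randomised, such as patients graded mrTRG 3–5, or patients who gave permission at restaging but were then not allocated. These have no allocated arm and cannot be placed in a comparison of LE with TME.

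**4. Restricted reading.** Modified ITT = the part of *C* inside *R*, which is *R*. Patients removed from ITT: 0.

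**5. Result.** On the first reading the set is larger than ITT, and on the second it equals ITT. On neither is it a smaller set drawn from ITT.

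**6. Comparison of wordings.** The per-protocol definition is expressly limited to patients in the ITT group. The modified ITT definition has no such limit, so the restricted reading has to be supplied by the reader.

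**7. Powered population.** Sample size calculation allocates 67 patients to each group, 2 × 67 = 134, and plans to enrol 140 after dropout. These are allocated patients, so the population that was sized is *R*.

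**8. How many extra patients?** If a share *f* of pre-CRT patients is mrTRG 1 or 2 and all of them are randomised, the literal set holds 140/*f* patients, of whom 140/*f* − 140 are not randomised. The article does not give *f*. Purely by assumption:
- *f* = 0.20: 140/0.20 = 700, so 700 − 140 = 560 not randomised
- *f* = 0.60: 140/0.60 ≈ 234, so 234 − 140 = 94 not randomised

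On the restricted reading the number is 0 whatever *f* is. The range reflects only the assumption, and the finding does not use it.

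**9. Does another provision settle it?** No. Even on the restricted reading, the experimental-arm rule moves some LE patients to the TME group and drops others. No sentence states that the endpoints are analysed by allocated arm.

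**The case against.** The strongest reply is that the restricted reading is the natural one. Permission and serial numbers come after pre-CRT, only mrTRG 1 or 2 patients are eligible and allocated, the trial is sized at 140, and a patient without an arm cannot enter a two-arm comparison. On that view the label is redundant and the analysis is on all randomised patients. Much of this stands: the randomised comparison may well survive. What does not stand is that the text says so. It gives the two sets different definitions and prefers the modified one for the endpoints.

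A second reply is that undergoing pre-CRT could mean completing the regimen, which would remove randomised patients with incomplete treatment. That would escape both readings, but the article does not say it.

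A third is that a wider pre-CRT set could suit the mrTRG accuracy endpoint, since a negative predictive value needs patients outside mrTRG 1 or 2 unless grade 2 counts as negative. That is a fair reason to give that endpoint its own population. It is no reason to use the set for the primary endpoint.

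Condensation into an article is no answer either, because the rule is stated outright rather than left out.

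In the other direction, a reader might infer that the primary comparison has lost its randomised denominator and that most of the set would be non-randomised poor responders having TME. The documents do not support this. The loss occurs only on the literal reading, no mrTRG share is given, and the article does not describe how patients outside the trial are treated.

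**Conclusion.** The point holds as a defect of definition. The set named for the primary and secondary endpoints either admits patients who were never allocated or duplicates ITT, and it does not work as a modified ITT set in either case. This follows from the article's own sequence of pre-CRT, restaging and randomisation, and needs no outside figure. It assumes only that eligible randomised patients have had pre-CRT, which the eligibility rule ensures.

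No numerical size can be attached: the count of non-randomised patients is not derivable from the document and is zero on the restricted reading. The wording may be a drafting slip, but the article does not say what was meant. Because it governs the primary analysis, it should be corrected before the data are analysed.

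**What to change.** - **Data analysis.** State that the primary endpoint and all between-arm secondary endpoints are analysed in the ITT set, meaning all randomised patients by allocated arm. Delete the modified ITT set, or redefine it by a post-randomisation criterion applied equally to both arms and use it only as a sensitivity analysis.
- **Investigational treatment of the experimental arm.** Reconcile this section for analysis purposes only, so that patients allocated to LE who go on to TME, or who decline it, stay in the LE arm in the ITT analysis. The clinical recommendation itself is not touched.
- **Secondary study endpoints, item 4.** State the population for mrTRG accuracy separately, since it is not a between-arm comparison.

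The cost is a few sentences across three sections. Sample size, allocation and treatment do not change. Follow-up of patients who decline TME is already planned; their data would be analysed with the LE arm instead of being set aside.

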#### Primary outcome

The primary endpoint of the current study is the rate of postoperative complications. Postoperative events occurring up to 30 days after surgery will be evaluated by the Clavien-Dindo Classification, any events grade 2 or higher will be considered postoperative complications.

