### Safety

The main outcome will be the detection and documentation of postoperative complications. The severity of complications will be classified according to the Clavien-Dindo Classification Grade and will be registered in the case reporting form. Currently, the oncologic outcome of pre-CRT followed by LE is considered to be equivalent to that of pre-CRT followed by TME for patients who respond well to pre-CRT. If the pathologic results show ypT2 with risks, ypT3 or ypT4, surgeons will recommend to perform TME for oncologic safety of the participants. The current study will meet with all local legal requirements and meet all requirements of the ICH Guideline for Clinical Safety Data Management, Definition and Standards for Expedited Reporting, Topic E2A.

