In terms of postoperative complications, only one patient (2.1%) in our previous study developed a postoperative complication (perianal fistula) that required prolonged hospitalization [27]. In a recent prospective study of LE in patients with T2 rectal cancer, surgery-related adverse events above grade 3 occurred in 16 patients (21%) and grade 1 or 2 complications occurred in 50 patients (65%) [26]. Although complications of LE after pre-CRT are generally less severe than complications of TME, the rate of overall complications including dehiscence of the rectal suture line resulted from anal pain are higher than TME after pre-CRT [26]. Based on the assumption that the oncologic outcomes of LE and TME are similar for patients with a favorable response (mrTRG 1 or 2) after pre-CRT, further prospective studies on surgical outcomes in LE after pre-CRT are needed.

Pre-CRT followed by LE causes minimal loss of anorectal function and quality of life, similar to watchful waiting [26]. TME results in postoperative loss of anorectal, urinary and sexual function, and also carries the risk of permanent stoma formation [10]. In mid-to-low advanced rectal cancer, the use of pre-CRT has decreased the rate of permanent stoma formation; however, in our recent study, approximately 30% of patients receiving TME after pre-CRT did develop a permanent stoma [27]. A recent prospective study suggested that pre-CRT followed by LE might be an alternative to TME for patients with rectal cancer who have a favorable response to pre-CRT or who seek organ preservation because the Fecal Incontinence Severity Index (FISI) score and the Functional Assessment of Cancer Therapy-Colorectal (FACT-C) scores did not substantially decrease after surgery [26].

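### The per-protocol set drops patients with serious adverse events, so the subgroup results it feeds are selected on post-randomisation events related to outcome

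*Protocol article*

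**What the plan says.** All the relevant text is in the protocol article.

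- **Base definition of the PP set (Data analysis).** "The per protocol (PP) analysis set will include only the subjects in the ITT group who complete the study protocol".
- **Further exclusions (Data analysis).** "Patients who withdraw informed consent or who develop serious adverse events will be excluded from the PP analysis set". No time window, causal link or breach of protocol is required.
- **Use of the PP set (Data analysis).** "The PP analysis set will be used for subgroup analysis". No other use is stated.
- **Set for the main analyses (Data analysis).** "The modified ITT set will be used for analysis of primary and secondary study endpoints".
- **Primary endpoint (Primary outcome).** Events up to 30 days after surgery are graded by Clavien-Dindo, and "any events grade 2 or higher will be considered postoperative complications".
- **Safety.** "The main outcome will be the detection and documentation of postoperative complications". A serious adverse event is not defined in the text. The section says only that the study will "meet all requirements of the ICH Guideline for Clinical Safety Data Management, Definition and Standards for Expedited Reporting, Topic E2A".
- **Subgroup outcome (Secondary outcomes measures).** The one subgroup item listed is oncologic outcome in patient subgroups. The oncologic outcomes named in that section are 3-year disease-free survival, 3-year overall survival and recurrence.

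**The concern.** A per-protocol set should select on conduct: whether the patient was eligible, had the allocated operation and was assessed. A patient who met all of that and then had a serious complication followed the protocol and supplied an endpoint. Removing that patient selects on what happened after randomisation.

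Here the reason for removal is also close to what is being measured. The Safety section treats postoperative complications as the main outcome, so the serious ones are at once primary-endpoint events and grounds for exclusion. For complication results in the PP set, the rule takes the worst events out of the numerator and those patients out of the denominator.

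For the oncologic subgroups the mechanism differs. The rule has no time limit, so on a plain reading a death recorded as a serious adverse event during the 3-year follow-up leaves the set, and with it an overall-survival and disease-free-survival event. Non-fatal serious events remove patients for a reason that may differ between the arms, which breaks randomised comparability within the subgroup.

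At stake is whether subgroup statements about the safety and survival of LE would rest on a population from which the patients with the worst courses had been taken out.

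**Working it through.** **Plan's own figure.** The article gives no figure for the PP set or for the share of endpoint events that are serious, so there is nothing of that kind to reproduce. The planned 67 per group is used below only as the arm size. The usual formula gives 2 × 0.15 × 0.85 × (1.645 + 0.842)² / 0.15² ≈ 70.1, so 71 per group. At 67 the power is about 78.4%. That is a separate, small matter and nothing below depends on it.

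**Inputs from the document (Sample size calculation).** 15% in each arm, a margin of 15 points, one-sided 0.05, 67 per group.

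**Assumption.** s is the share of primary-endpoint events that are serious adverse events. It is not in the document, so a range is shown. Only the overlap with the 30-day endpoint is modelled; serious events that are not endpoint events are ignored.

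**Formula.** If p is the true complication rate, a fraction ps of the patients is removed. All of them had events, so

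PP rate = p(1 − s) / (1 − ps).

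**Case A: LE worse by exactly the margin (30% vs 15%), equal shares**

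| s | LE in PP set | TME in PP set | Difference |
|---|---|---|---|
| 0 | 30.0% | 15.0% | 15.0 points |
| 1/3 | 0.20/0.90 = 22.2% | 0.10/0.95 = 10.5% | 11.7 points |
| 1/2 | 0.15/0.85 = 17.6% | 0.075/0.925 = 8.1% | 9.5 points |
| 2/3 | 0.10/0.80 = 12.5% | 0.05/0.90 = 5.6% | 6.9 points |

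**Case B: both arms at the planned 15%, equal shares.** The expected difference is zero for any s, but the rates are understated: 11.7% at s = 0.25, 8.1% at 0.50 and 4.2% at 0.75. With 134 patients and 134 × 0.15 ≈ 20 events, about 5, 10 and 15 patients are removed.

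**Case C: both arms at 15%, TME events more often serious (s = 0.25 LE, 0.75 TME)**

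- LE: 0.1125/0.9625 = 11.7%
- TME: 0.0375/0.8875 = 4.2%
- Difference: a false excess of 7.5 points against LE.

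**What a non-inferiority test in this set would do.** The plan schedules no such test; this only shows how far the set can mislead. It was simulated with 67 per arm and 200,000 runs, declaring non-inferiority when the one-sided 95% Wald upper limit is below 15 points.

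| True LE / TME | s, LE / TME | Expected PP difference | Chance of declaring non-inferiority |
|---|---|---|---|
| 30% / 15% | 0 / 0 | 15.0 points | 5.1% |
| 30% / 15% | 0.25 / 0.25 | 12.6 points | 10.5% |
| 30% / 15% | 0.50 / 0.50 | 9.5 points | 24.7% |
| 30% / 15% | 0.75 / 0.75 | 5.5 points | 63.2% |
| 15% / 15% | 0 / 0 | 0 | 78.5% |
| 15% / 15% | 0.25 / 0.75 | 7.5 points | 49.4% |

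The rule can make a poor result look acceptable or an acceptable one look poor, depending on shares that the document does not give.

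**The case against.** The strongest reply is that the rule does not touch the trial's conclusion. That stands. Primary and secondary endpoints go to the modified ITT set, the PP set has one stated use, and no PP non-inferiority test is planned. A reader might infer that the main comparison is biased by this exclusion; the text does not support that.

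A reader might also infer that the exclusion pulls the arms together and so favours non-inferiority. That holds in Case A, where LE is truly worse and the serious shares are equal. The Discussion points to unequal shares: "Although complications of LE after pre-CRT are generally less severe than complications of TME". The same sentence adds that the overall complication rate is higher with LE. If TME events are the more serious, more of them are removed and LE looks worse, as in Case C. No direction can be claimed.

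Two further strong readings fail. One is that serious adverse events are largely the primary outcome itself. The overlap in kind is clear, but its extent is not documented: the article does not write out what counts as serious, some endpoint events may not be serious, and some serious events may be late or unrelated to surgery. The local-excision study described in the Discussion (16 patients with events above grade 3, 50 with grade 1 or 2) gives only a rough guide: 16/66, about 24%, if those patients are distinct. The other is that every subgroup result is selected on its own outcome. The listed subgroup outcome is oncologic. Selection on that outcome is direct only for deaths counted as serious adverse events; otherwise the harm is loss of comparability.

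The unseen analysis plan does not answer the point. The exclusion is stated in the article, and a plan that followed it would carry it forward.

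**Conclusion.** The point holds in limited form. The PP set is defined partly by a post-randomisation event that is not a deviation from protocol and that overlaps the primary endpoint, and subgroup analysis is assigned to that set. PP and subgroup results are therefore selected on events related to outcome.

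The bias is of unknown size and direction. In the scenarios shown, it ranges from shrinking a true 15-point difference to between 11.7 and 6.9 points (equal serious shares of one third to two thirds) to creating a false 7.5-point excess against LE where none exists (shares of 25% and 75%). All of these rest on assumed shares. The survival part rests on reading the rule, as written, to cover serious events at any time, fatal ones included.

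The main primary and secondary analyses are unaffected by this rule. The oncologic subgroup item is itself on the secondary list; the reading here is that the specific sentence on subgroups governs it. The defect should be corrected, but it ranks below those that put the primary conclusion at risk.

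**What to change.** 1. In Data analysis, delete the serious-adverse-event criterion from the PP exclusions.
2. Define the PP set by conduct only: eligible, received the allocated operation, and assessed at 30 days. State that no postoperative event is a ground for exclusion.
3. Run subgroup analyses in the ITT set, which the article already defines as all randomised patients.

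A supportive non-inferiority bound in the redefined PP set would be reasonable but is optional.

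The cost is a change of wording in one paragraph. Sample size, recruitment and data collection do not change. The optional bound would add one table. The change should be made and dated before the outcome data are analysed.

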### Study design

A prospective, double-arm, randomized, open-labeled, single center, clinical trial was initiated at Asan Medical Center, Seoul, Korea beginning in July 2017. (Fig. 1).

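### The non-inferiority claim rests on the modified ITT set alone: no adherence-based check is stated, and the per-protocol set is kept for subgroups

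*Protocol article*

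**What the plan says.** Sample size calculation (Protocol article) frames the primary question as non-inferiority, with "a significant level of 0.05, one-sided", assumed complication rates of "15% in the TME group and 15% in the LE group", a 15-point margin, and "a total of 67 patients should be allocated to each group". Study design describes "A prospective, double-arm, randomized, open-labeled, single center, clinical trial".

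Data analysis defines three sets:
- **ITT:** everyone randomised to a surgery group.
- **Modified ITT:** everyone who undergoes preoperative chemoradiotherapy, a step that precedes randomisation. Nothing says these patients are grouped by allocated arm.
- **Per-protocol (PP):** ITT patients who complete the protocol, without those who withdraw consent or develop serious adverse events.

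It then assigns them: "The modified ITT set will be used for analysis of primary and secondary study endpoints", and "The PP analysis set will be used for subgroup analysis". The ITT set is named only for baseline characteristics.

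Investigational treatment of the experimental arm adds a grouping rule. LE patients who are recommended TME on pathology and have it are counted in the TME group. Those who decline it leave the study and are followed for a subgroup analysis.

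**The concern.** In a superiority trial, keeping patients who had the other arm's operation usually works against the claim. In a non-inferiority trial it works for the claim, because the two observed rates move towards each other. An analysis by adherence is therefore the usual companion to the randomised comparison, and here the text sends the PP set elsewhere.

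Refusal of the allocated operation is plausible. The trial is open-label, patients are randomised after a good MRI response, and the alternative to organ preservation is an operation for which the Background lists leak, sexual and urinary dysfunction and stoma. At stake is a non-inferiority conclusion partly produced by patients who had the other operation, with no stated analysis of the primary endpoint that would show it. Separately, subgroup comparisons lose the protection of randomisation.

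**Working it through.** **Inputs.** From Sample size calculation: 67 per arm, TME rate 15%, margin 15 points (so LE 30% at the boundary), one-sided 0.05. Assumed, because the documents do not give them: the switching fraction c (0 to 20%), a Wald upper confidence limit as the decision rule, and that a patient who switches takes on the complication rate of the operation received.

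**1. The plan's own figure.** With unpooled variance, n = (1.6449 + 0.8416)² × (2 × 0.15 × 0.85) / 0.15² = 6.1827 × 0.255 / 0.0225 = 70.07, so 71 per arm. The stated 67 is not reproduced; power at 67 is 78.4%. This is a separate matter, and 67 is used below.

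**2. Rates under switching, analysed as allocated.** TME arm: 0.15 + 0.15c if a fraction c of TME patients have LE. LE arm: 0.30, or 0.30 − 0.15c if the same fraction of LE patients have TME. Non-inferiority is declared when p_LE − p_TME + 1.645 × √[p_LE(1 − p_LE)/67 + p_TME(1 − p_TME)/67] < 0.15.

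Example, c = 10%, TME to LE only, normal approximation:
- Rates are 0.30 and 0.165, difference 0.135.
- SE = √[(0.2100 + 0.1378)/67] = 0.0720.
- Probability of declaring non-inferiority = Φ(0.015/0.0720 − 1.645) = 7.5%. Exact binomial enumeration gives 7.7%.

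**3. False non-inferiority rate, exact enumeration.**

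| Switching c | TME to LE only | Both directions |
|---|---|---|
| 0% | 5.2% | 5.2% |
| 5% | 6.4% | 7.8% |
| 10% | 7.7% | 11.3% |
| 20% | 11.0% | 21.3% |

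Switching from LE to TME only gives similar figures (6.4%, 7.9%, 11.6%). The Farrington-Manning test agrees closely (7.6% one-way and 11.1% two-way at c = 10%). The sample-size sentence also calls the test two-sided. At one-sided 0.025 the rate is 2.6% with no switching, and 6.3% and 13.2% at 10% and 20% two-way.

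**4. Would the PP set as written protect the claim?** If a share s of complications are serious adverse events and those patients are dropped, a rate p becomes p(1 − s)/(1 − ps). For s = 25%: LE 0.225/0.925 = 24.3%, TME 0.1125/0.9625 = 11.7%, difference 12.6 points against a true 15. With no switching at all, the false non-inferiority rate (normal approximation) is 6.4%, 9.8% and 22.6% for assumed shares of 10%, 25% and 50%. So this set does not restore 5%.

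**5. The regrouping rule.** The Background gives a projected completion TME rate of 25.6% in mrTRG1. Suppose, as an assumption, that it applies to the whole LE arm and those patients are moved to the TME group. At the same boundary the rate is 5.0% if only their complications after TME count (15%). It is 10.6% if their complications after LE move with them (30%): the TME group rate is then (0.15 + 0.256 × 0.30)/1.256 = 18.1%. The rule therefore needs settling alongside the analysis sets.

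**The case against.** The strongest objection is that the excess is conditional. A reader might infer that the trial's error rate is above 0.05. The documents do not show that: the 5% in Sample size calculation is dropout, no switching rate is given, and with no switching the rate is 5.2%. The Discussion adds that most patients are restaged two or three days before surgery, which in practice leaves little time to change operation. This stands, although it does not rule out refusal.

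The larger, two-way figures have less support. The reasons for refusal point to TME patients wanting LE, and nothing suggests that LE patients would choose TME at the same rate. The one-way column is the fairer guide. Nor is the 25.6% completion TME rate a switching rate: those patients received the LE they were allocated, so an analysis as allocated would not dilute the 30-day LE rate.

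A reader might also infer that the sets are simply reversed and that PP should be primary. Step 4 shows why that would not help as PP is now defined. In addition, the dilution argument assumes analysis as allocated, which the modified ITT definition does not state and which the regrouping rule contradicts for some LE patients. That narrows the claim but gives another reason to rewrite the section.

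Lastly, the article is condensed, and a PP run of the primary comparison may sit in a fuller document. The Wald rule is likewise an assumption; the article names chi-square and Fisher tests. However, the article does not leave the sets open. It assigns each one, and the point rests on that assignment.

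**Conclusion.** The point holds in conditional form. For a non-inferiority question, the article names the modified ITT set alone for the primary endpoint and keeps PP for subgroups. No adherence-based check of the claim is stated, and subgroup comparisons use a post-randomisation set.

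If patients are analysed as allocated and some have the other operation, the false non-inferiority rate exceeds 0.05. The excess over 5.2% is 1.2, 2.5 and 5.8 points at 5%, 10% and 20% one-way switching, and 2.6, 6.1 and 16.1 points if switching runs equally both ways. These sizes rest on assumed switching rates, true rates at the margin, 67 per arm and a Wald limit. An actual breach of 0.05 is not established. The problem should be corrected because correction is cheap, but the size of its effect in this trial is unknown.

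**What to change.** In Data analysis:

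1. Replace the sentence giving the primary endpoint to the modified ITT set with one stating that the primary non-inferiority comparison uses all randomised patients, by allocated arm.
2. Define PP by receipt of the allocated operation, and delete the exclusion for serious adverse events, so that membership does not depend on complications.
3. Repeat the primary comparison in that PP set. Claim non-inferiority only if the upper confidence limit is below 15 points in the randomised set and the PP result is consistent with it, with the meaning of consistent fixed in advance.
4. Run subgroup analyses in the randomised set.

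In Investigational treatment of the experimental arm, reconcile the analysis-group wording with this: for the primary comparison, LE patients who go on to TME, or who decline it, stay in the LE arm. This concerns only how patients are counted; the clinical recommendation is unchanged. All these edits are needed together, since changing the PP sentence alone would leave the other rules in conflict with it.

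The cost is wording and one further analysis of data already collected. The PP set is somewhat smaller, so its interval is slightly wider and the claim slightly harder to make.
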